### Concomitant therapy/medications

Patients will receive immunosuppression according to hospital protocols and other medications as necessary for their comorbidities and current clinical condition. Their postoperative care will be the same as if they had undergone a standard liver transplant.

## Objectives and outcome measures

### Primary

There are two linked primary objectives and respective outcome measures:

Primary objective: (A) Establish the feasibility of NMP-L to increase the number of transplantable livers.

Primary Outcome measure: (A) ‘Rescue rate’ that is, the proportion of rejected livers that can be used for transplantation having been deemed viable following a period of machine perfusion.

Primary objective: (B) Achieve successful transplantation of previously rejected donor livers following viability testing using NMP-L.

Primary outcome measure: (B) 90-day patient survival, calculated as the number of patients alive 90-day post-NMP-L-treated marginal liver transplantation (numerator) divided by the total number of NMP-L-treated marginal liver transplants performed (denominator).

### Secondary

Secondary objective (1): Assessment of liver graft function following transplantation (by incidence of primary non-function and early allograft dysfunction).

Secondary outcome measures (1): Liver function tests; 90-day graft survival; 12-month patient and graft survival.

Secondary objective (2): Assess morbidity associated with receipt of extended criteria graft that had previously been rejected.

Secondary outcome measures (2): Adverse event rates and severity, graded according to the Clavien-Dindo classification^40^ (see online supplementary file 1); Requirement of renal replacement therapy; incidence of biliary complications (including incidence of ischaemic-type biliary lesions diagnosed on magnetic resonance cholangiopancreatography (MRCP) at 6 months); incidence of vascular complications; biopsy-proven acute rejection; reoperation rate; length of intensive therapy unit stay and length of hospital stay.

10.1136/bmjopen-2017-017733.supp1Supplementary file 1

Secondary objective (3): Assess the physiological response to reperfusion of the perfused grafts.

Secondary outcome measures (3): Postreperfusion syndrome, defined as a decrease in mean arterial pressure (MAP) of more than 30% from the baseline value for more than 1 min during the first 5 min after reperfusion (assessed in the context of inotrope use).

Secondary objective (4): Identify impact on quality of life (QoL) after transplantation with these liver grafts.

Secondary outcome measures (4): Quality of life by delivery of the EuroQoL 5 Dimensions 5 Levels questionnaire at baseline, day 30 and 6 months post-transplant.

## Analytical methods

### Histopathology

Two independent liver histopathologists from UHBFT will perform all the histopathological assessments. Both will be blinded to the graft type and the primary and secondary outcome measures although the presence or absence of a postreperfusion biopsy means they will know whether a graft has met the criteria for transplantation. The histological analysis will be established using H&E at two levels as well as periodic acid Schiff, periodic acid Schiff diastase, haematoxylin van Gieson, reticulin, orcein, rhodanin and Perls stains of formalin-fixed paraffin-embedded liver tissue.

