**Figure 1 F1:**
[figure not shown]
Patient and donor liver pathways. HA, hepatic artery; PV, portal vein; UHB, University Hospitals Birmingham; VITTAL, Viability testing and transplantation of marginal livers.

**Table 2 T2:** Trial sample collection schedule

Perfusate samples	Hepatic arterial and hepatic venous biochemistry (point of care)	Preperfusion Every 30 min during perfusion	Cobas point-of-care desktop analyser
	Perfusate supernatant	Preperfusion Every 15 min for first hour Every hour thereafter	5×1 mL aliquots Stored at −80°C
Liver samples	Liver biopsy	L1 Preperfusion L2 After 4 hours L3 at end of perfusion* L4 Postreperfusion	16 G core needle biopsy Divided into segment for formalin, segment for frozen and piece for electron microscopy
	Common bile duct	CBD1 Preperfusion CBD2 Postreperfusion	Formalin
Bile samples	(If produced)	B2 sample at 2 hours B4 sample at 4 hours B6 sample at 6 hours	Total volume recorded and 2 mL samples snap frozen at these time-points
Patient samples	Biochemistry haematology clotting	Visits 1, 2, 3, 4, extended follow-up	Standard of care
	Serum, plasma, mononuclear cells (PBMC)	Visit 1 (preoperative (postinduction of anaesthesia), postreperfusion day 4 postoperative) Visits 2, 3, 4,	Additional research samples
	Urine	Visit 1 (pre-operative [post-induction], postreperfusion Day four post-op)	Additional research samples

*If lasting longer than 6 hours.

PBMC, peripheral blood mononuclear cell.

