There are undoubtedly some livers that will not be salvageable or ever safe to transplant. It is important for the purposes of the trial to include organs that fail to meet the defined viability criteria to compare these with transplantable high-risk livers. The research work package linked with the trial was designed to identify sensitive point-of-care liver quality tests and propose novel biomarkers or panels associated with viable livers.

The primary end-point of 90-day patient survival has been chosen as it is a nationally accepted, monitored and continuously audited outcome following liver transplantation. Obviously, the graft survival rate is important and for the trial to truly be successful, patients who reach the primary end-point should have a VITTAL graft still in situ. This will be considered when the DMC monitor the results at the interim analyses.

As well as the study design, challenges with trial logistics were also identified. One of the previously unseen difficulties after discussion with the haematology team is the issuing of packed red cells matched to the intended recipient, potentially before the patient is admitted to hospital, to avoid delaying the start of the perfusion. When patients are listed, they undergo a blood cross-matching process to identify blood group and the presence of antibodies. This sample is not held for longer than 7 days by the hospital and so if they are admitted for a transplant or require blood products for some other intervention, they have a new sample sent before those products are issued. In the case of the VITTAL trial, a perfusion may need to commence before the patient is admitted to hospital as they may have to travel some distance. Minimising the cold ischaemic time of marginal grafts is paramount to improve the chances of graft salvage. Therefore, in this scenario, blood is issued for the trial based on the results of the original sample and a repeat is sent when the patient is admitted to check they have not subsequently developed new antibodies. Blood product traceability is an important consideration and the blood products are documented to have been used in the device perfusate only and have not been used for recipient transfusion.

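### The post-reperfusion biopsy tells the histopathologists each liver's viability result; coded reading would avoid this for samples taken before transplantation

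*Protocol article*

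**What the plan says.** Under Analytical methods, Histopathology, the protocol article states: "Two independent liver histopathologists from UHBFT will perform all the histopathological assessments". On blinding it says: "Both will be blinded to the graft type and the primary and secondary outcome measures". The same sentence then makes an exception: "the presence or absence of a postreperfusion biopsy means they will know whether a graft has met the criteria for transplantation".

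Table 2 gives the liver biopsy times as "L1 Preperfusion L2 After 4 hours L3 at end of perfusion* L4 Postreperfusion", with a footnote on L3: "If lasting longer than 6 hours". The bile duct samples are "CBD1 Preperfusion CBD2 Postreperfusion".

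Under Objectives and outcome measures, primary outcome A is the rescue rate, defined as "the proportion of rejected livers that can be used for transplantation having been deemed viable following a period of machine perfusion". The Discussion calls it important "to include organs that fail to meet the defined viability criteria to compare these with transplantable high-risk livers".

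**The concern.** The blinding statement covers the primary outcomes, but its exception gives away one of them. A reader who knows that a liver met the transplant criteria knows that liver's contribution to outcome A.

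This matters if the slides are used to compare livers that failed viability testing with those that passed. The person scoring would then know the grouping variable, and any judgement in the scoring could follow that knowledge. The article accepts this as a consequence of the sampling. The sampling forces it only for tissue that exists solely after transplantation.

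**Working it through.** The article gives no figure on this point, so the check sets its sections side by side.

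1. **Is viability status a primary outcome?** Yes. The Primary analysis section puts the number of perfused grafts meeting the viability criteria in the numerator of the rescue rate. Whether one graft met them is therefore the per-liver result of outcome A. The biopsy does not reveal outcome B: an L4 sample shows that a transplant took place, not that the patient was alive at 90 days. The blinding gap concerns A only.

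2. **Which samples reveal it?** From Table 2:
   - L1 and CBD1 are taken before perfusion, and L2 after 4 hours. None is conditional on transplantation.
   - L3 is taken at the end of perfusion, only if perfusion exceeds 6 hours. It also precedes transplantation, but it is not neutral. Perfusion of the graft assesses viability within 4 hours and keeps a graft destined for transplantation on the machine until the recipient's explant is done. A failed graft has no such reason to stay on, so the existence of an L3 slide could itself hint at the result.
   - L4 and CBD2 are post-reperfusion and exist only for transplanted livers.

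3. **Is the unblinding forced?** For L4 and CBD2, yes. For L1, L2, L3 and CBD1, no: a missing L4 is informative about an L1 slide only if the reader can link the two to the same liver. Without that link, and with the earlier slides scored first, the information is not available. The tissue is formalin-fixed and paraffin-embedded, and Storage of samples says that blocks are kept after sectioning and staining, so coded batch reading looks practicable.

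4. **What could it bias?** Let D be the true mean difference in a histological score, non-viable minus viable. Let s0 and s1 be the average shifts in scoring when the reader knows that a liver failed or passed. The observed difference is then

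   observed = D + (s0 − s1).

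   Blinded reading gives s0 = s1 in expectation, and the extra term vanishes. The article gives neither s0 nor s1, so the size of the term cannot be derived. If higher scores mean worse tissue and readers expect worse tissue in failed livers, then s0 > s1 and a true difference in that direction is exaggerated. That is an assumption about reader behaviour, not a result.

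5. **How many livers are involved?** Up to 53 are to be perfused (Sample size justification). At the desirable rate of 50%, 0.50 × 53 = 26.5 would be viable and 26.5 not. At the undesirable rate of 30%, 0.30 × 53 = 15.9 would be viable and 37.1 not. These counts show how many livers could be read with knowledge of the result. They are not an effect size.

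6. **What does it leave untouched?** The viability criteria are lactate, bile, pH, glucose, vessel flows, and the graft's perfusion and consistency. None is read from these slides. Ninety-day survival is vital status. The go/no-go rules use only these two outcomes. Acute rejection proven on biopsy, a secondary measure, arises only in recipients, so blinding the earlier samples to viability does not bear on it.

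**The case against.** The strongest case on the other side has four parts.

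- **The limitation is disclosed.** The exception stands in the same sentence as the promise, so nobody is misled. That is true, but disclosure does not make an avoidable exception necessary.
- **Reading order and slide labelling are laboratory detail** that a condensed article may leave to the full protocol. This would answer a complaint that coding is not described. It does not answer the present point, because the article states the outcome of its procedure: the readers will know.
- **The comparison in the Discussion is not identified as histological.** It refers to point-of-care tests and biomarkers, and the Histopathology section lists stains but no grading scale. This stands. The risk attaches to any histological comparison of the two groups, and the article does not specify one.
- **The effect is not quantified.** This stands too.

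A reader might infer that all biopsies from a graft are read together. The article does not say so; it says only that the biopsy's presence or absence is revealing.

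**Conclusion.** The point holds as a limited one. Blinding to the primary outcomes fails for outcome A by the article's own account, and this is avoidable for L1, L2, CBD1 and, where it exists, L3. It could bias a histological comparison of non-viable with transplanted livers by an amount that cannot be derived. Exaggeration of the difference is plausible but not shown.

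Three stronger readings are tempting, and the document supports none of them:

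- That the primary results are compromised. Neither co-primary outcome nor any stopping rule uses these slides.
- That the direction of bias is known. It depends on an assumption about how the readers behave.
- That the remedy is free. The article gives no cost information, and coding takes some effort and time.

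The conclusion assumes that histology will be compared between the two groups in some form and that its scoring involves judgement. This is a cheap improvement, not a flaw that threatens the trial's main conclusions.

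**What to change.** Amend the Histopathology section as follows:

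- Give every slide a random code with no liver identifier, so that the set of slides belonging to a liver, including whether L3 exists, is hidden.
- Have the same two histopathologists read L1, L2, L3 and CBD1 in random order, and lock those scores before L4 and CBD2 are released.
- State that L4 and CBD2 readings cannot be blinded to viability, and limit the blinding claim for outcome A to the earlier samples.

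The slides and readers stay the same. Someone other than the readers must hold the code, changes within a liver are worked out from the locked scores once the code is broken, and final histology reports come slightly later. No sample size, outcome definition or decision rule changes.

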### Perfusion, clinical and laboratory data

Donor and patient demographics as well as intraoperative data will be collected. Body mass index (BMI) was defined as weight in kilograms divided by the square of the height in metres (kg/m^2^). In non-heart beating (DCD) donation, FWIT is defined as the time between the systolic blood pressure of the donor dropping below 50 mm Hg until the point of aortic perfusion. Cold ischaemic time is defined as the time between aortic perfusion and the start of NMP-L. DRI and Balance of Risk (BAR) will be calculated as per the relevant literature.^11 41^

The perfusate fluid will undergo point-of-care biochemical testing every 30 min as previously described. Perfusate will be taken at the time-points described in table 2 and tested for transaminase, urea, albumin and factor V levels. Patient’s blood samples will be analysed for full blood count, urea, creatinine and electrolytes, liver function tests, prothrombin time, amylase, C-reactive protein and plasma glucose using standard laboratory methods (Roche Modular system, Roche, Lewes, UK) both preoperatively and postoperatively. Research recipient blood and urine samples will also be taken as part of WP2 that will enable immune cell profiling as well as lipodomic, proteomic and metabolomic testing.

### Patient questionnaires

QoL will be assessed by delivery of the EQ-5D-5L questionnaire (UK (English) 2009 EuroQol Group EQ-5D is a registered trademark of the EuroQol Group) at baseline, day 30 and 6 months’ post-transplant. EQ-5D-5L is a five-level version of the EQ-5D descriptive system (Herdman *et al*. Qual Life Res DOI 10.1007/s11136-011-99031). The 5L retains the 5-dimensional (5D) structure of the original EQ-5D-3L but the levels on each dimension were expanded to five based on qualitative and quantitative studies conducted by the EuroQol Group. Index-based values (‘utilities’) enable the calculation of quality-adjusted life years which help inform economic evaluations of healthcare interventions.

## Statistical justification and outcome analysis

### Sample size justification

For (A) feasibility of NMP-L to rescue discarded liver grafts, it is anticipated that NMP-L will achieve a desirable organ recovery rate of at least 50%, with an undesirable rate of 30% or less as this would not be considered economically feasible. The significance level (α) is set at 0.05, corresponding to the probability of incorrectly rejecting the hypothesis given it is true (type I error), and the power is set at 0.90 (type II error rate, β=0.10), corresponding to the probability of correctly deciding the NMP-L treatment is successful given the true response rate is greater than 50%.

Using a Simon’s two-stage design^38^:

Interim assessment stage 1A of accrual: 24 marginal grafts will be perfused and assessed in the first stage. Grafts will be transplanted depending on the criteria achieved. The procedure will be considered infeasible if there are fewer than eight recovered livers. If more than eight livers are transplanted, we will proceed to Stage 2A.

Final stage 2A of accrual: Up to additional 29 marginal grafts will be perfused. We would consider the procedure feasible if there are at least 22 recovered livers out of 53 perfused livers.

For (B) for viable livers transplanted following NMP-L, a desirable 90-day patient survival rate is at least 88%, with an undesirable rate of 73% (15% lower). The mean 90-day patient survival rate for ‘standard’ liver transplants is 93%.^42^ An optimal three-stage design^39^ will be used to test the null hypothesis that the mean 90-day patient survival rate will be less than 73% (p≤0.73) versus an alternative hypothesis that the 90-day patient survival rate will be at least 88% (p≥0.88). The significance level is set at 0.20 (target α=0.2), giving a 0.2 probability to conclude that a single transplantation is viable when it truly is not viable. The power is set at 80% (target β=0.2), giving a 0.2 probability to conclude that a single transplantation is not viable when it truly is viable.

Interim assessment stage 1B: Following transplantation in three patients, the trial will stop early (concluding p≤0.73) if there are fewer than two patients achieving 90-day survival. If two or more patients reach the primary end point of 90-day survival, an additional eight transplantations will be performed.

Interim assessment stage 2B: Following transplantation in 11 patients (combined first and second stages) the trial will stop early (concluding p≤0.73) if there are 7 or fewer successes. If 8or more patients reach the primary end point, an additional 11 transplantations will be performed.

Final stage 3B: Following transplantation in 22 patients in all three stages, the trial will be successful if at least 18 patients reach the primary end-point of 90-day survival.

The trial schema is provided in figure 2.

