### Analysis of outcome measures

#### Primary analysis

To assess (A) the feasibility of NMP-L, the rescue rate will be calculated as the number of perfused marginal grafts meeting the criteria for viability (numerator) divided by the total number of perfused marginal grafts (denominator).

$$Rescue\;Rate=\frac{Number\;of\;viable\;perfused\;marginal\;grafts}{Total\;number\;of\;perfused\;marginal\;grafts}$$

To assess (B)—achievement of successful transplantation of previously rejected donor liver following viability testing using NMP-L. We will evaluate 90-day patient survival rate as an indicator of liver function and/or viability following transplantation of marginal liver grafts following NMP-L. The 90-day patient survival rate will be calculated as the number of patients alive at 90-day post-transplant with a VITTAL graft, divided by the total number VITTAL patients transplanted.

$$90\;day\;patient\;survival\;rate=\;\frac{Number\;of\;patients\;alive\;at\;90\;days\;post\;transplantation}{Total\;number\;of\;transplanations\;performed}$$

For (A), all livers undergoing NMP-L treatment will be included for evaluation in the interim and final analyses. For (B), all transplantations performed will be included for evaluation in the interim and final analyses. The rate outcomes will be reported together with confidence intervals using the Wilson (1927) method.^43^

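### The stage 1A rule leaves exactly eight of 24 livers without a decision, counts different things for stop and go, and misses the stated 90% power if 'more than eight' is applied

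*Protocol article*

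**What the plan says.** All design inputs for outcome A are in the protocol article under Sample size justification. The target is that "NMP-L will achieve a desirable organ recovery rate of at least 50"%. The rate to be ruled out, p0, is 30%, chosen on economic grounds. The article states that "The significance level (α) is set at 0.05" and "the power is set at 0.90 (type II error rate, β=0.10"). The design is introduced by "Using a Simon’s two-stage design": 24 livers in stage 1A, up to 29 more in stage 2A, and success at 22 or more recovered livers out of 53.

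The interim rule declares the procedure "infeasible if there are fewer than eight recovered livers. If more than eight livers are transplanted, we will proceed to Stage 2A".

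Outcome A is defined in two further places. Under Primary (Objectives and outcome measures) it is "the proportion of rejected livers that can be used for transplantation having been deemed viable" after perfusion. Under Primary analysis the numerator is "the number of perfused marginal grafts meeting the criteria for viability (numerator"), with all perfused grafts as the denominator. The section Planned interim assessments then relies on the go/no-go decisions as already clearly set out.

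**The concern.** There are two faults in one rule.

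- **A gap.** Fewer than eight means 7 or less, and more than eight means 9 or more. The value 8 falls in neither clause. The stage 1B and 2B rules for outcome B leave no such gap: each assigns every possible count to stop or go.
- **Two counts.** The stop clause and the final rule use recovered livers, the go clause uses transplanted livers, and the rescue rate uses livers that meet the viability criteria. In the section Perfusion of the graft, meeting the criteria makes a liver one to be considered, and the recipient goes to theatre only once the surgeon is satisfied. Viable and transplanted are therefore separate states.

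This rule decides whether a co-primary outcome goes on to its second stage. In an open-label single-arm trial, a result that the rule does not cover would have to be settled after the data are known, and the choice changes the power of the design.

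**Working it through.** **Inputs** (all from Sample size justification): p0 = 0.30, p1 = 0.50, α = 0.05, power 0.90, n1 = 24, n2 = 29, success at a total of 22 or more of 53.

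**Formula.** Let X1 be the stage 1 count and g the smallest count that leads to stage 2. Then

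P(success | p) = Σ from x = g to 24 of P(Bin(24, p) = x) × P(Bin(29, p) ≥ 22 − x).

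This is α at p = 0.30 and power at p = 0.50. The early-stop probability is P(Bin(24, p) < g).

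**Step 1: reproduce the plan's figures, and compare the two readings.**

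| Go from | α (p = 0.30) | Power (p = 0.50) | Early stop, p = 0.30 | Early stop, p = 0.50 |
|---|---|---|---|---|
| 8 | 0.0466 | 0.9017 | 0.565 | 0.032 |
| 9 | 0.0419 | 0.8734 | 0.725 | 0.076 |

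With go from 8, both stated targets are met. A search over two-stage designs with these error rates, with totals up to 75, gives this as the minimax design: stop at 7 or fewer of 24, fail at 21 or fewer of 53. With go from 9, power is 0.90 − 0.8734 = 0.027 below the stated value.

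**Step 2: how likely is exactly 8?** P(X1 = 8) = C(24, 8) × p^8 × (1 − p)^16, with C(24, 8) = 735,471.

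- p = 0.30: 735,471 × 0.3^8 × 0.7^16 = 0.160
- p = 0.40: 735,471 × 0.4^8 × 0.6^16 = 0.136
- p = 0.50: 735,471 / 2^24 = 735,471 / 16,777,216 = 0.0438

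**Step 3: tie the two together.** The power lost by stopping at 8 is P(X1 = 8) × P(Bin(29, 0.5) ≥ 14). The second factor is 0.5 + C(29, 14)/2^29 = 0.5 + 0.1445 = 0.6445. The loss is 0.0438 × 0.6445 = 0.0283, which agrees with 0.9017 − 0.8734 = 0.0283. The early-stop probability at p = 0.50 rises by the same 0.0438, from 0.0320 to 0.0758.

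**Step 4: could a lower boundary have been meant?** Go from 7 also meets both targets (α 0.0487, power 0.9120). Its expected sample size at p = 0.30 is 41.73, against 36.62 for go from 8, and it contradicts the stop clause. Every boundary that meets the stated power treats 8 as a go.

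**Step 5: where would go from 9 fit?** The same search gives the design with the smallest expected sample size at p = 0.30 as stop at 8 or fewer of 24, fail at 24 or fewer of 63 (α 0.0497, power 0.9033). A go condition of more than eight thus belongs with 63 livers, not 53. The document does not show whether that is how the wording arose.

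**Step 6: the two counts.** Suppose 9 livers of 24 are viable and 8 are transplanted. The stop clause is not met (9 recovered) and the go clause is not met (8 transplanted). Only viable livers are meant to be transplanted, so the transplanted count cannot exceed the viable count, and counting transplants can only make go harder to reach. The document gives no rate of viable livers left untransplanted, so this effect is not quantified.

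**The case against.** The best defence is that the only stop rule is fewer than eight, and 8 is not fewer than eight. Read that way, the go sentence is a sufficient condition and not a necessary one. The trial would continue at 8, with power 0.9017 and α 0.0466 as planned, and the fault would be a slip of 'more than' for 'at least'. A statistician could recover the intended boundary from the stated parameters. On the counts, the text links viability with transplantation, and Primary analysis defines the numerator explicitly. Figure 2, the trial schema, was not available for this review and may state the cut-off.

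Much of this stands. The shortfall in power arises only if 8 is treated as a stop. Type I error is below 0.05 on either reading, and the sample size and final threshold are correct. At the target rate of 50%, exactly 8 has only a 4.4% chance.

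It does not clear the rule. The go clause, read as the condition for proceeding, says something different from the stop clause, and the reader has to recompute the design to learn which one holds. A pre-specified rule should not need that. A correct Figure 2 would contradict the text, which would still need correcting. The explicit numerator in Primary analysis confirms that transplanted is the wrong count in the go clause.

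**Conclusion.** The point holds. Stage 1A has no decision at 8 of 24, and its two clauses count different things. If the go clause is applied as worded, power is 87.3% and not the stated 90%, and early stopping at a true rate of 50% goes from 3.2% to 7.6%. If 8 is a go, the stated design is right as it stands. The damage is to power and to the clarity of a co-primary decision, not to type I error.

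The figures assume independent livers with a common recovery rate, one count used throughout, and an interim rule that is followed. The correction should be made because the rule is binding for a co-primary outcome and the remedy is trivial.

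**What to change.** Replace the two stage 1A sentences with one rule: the procedure is considered infeasible if 7 or fewer of the 24 perfused livers meet the viability criteria, and the trial proceeds to stage 2A if 8 or more do. Use that count, livers viable by the criteria, at stage 1A, at stage 2A (22 or more of 53) and in the rescue-rate formula. Report the number transplanted separately. Check that Figure 2 gives the same cut-off.

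The cost is one sentence in the protocol, with the word for the count aligned at stage 2A. No liver is added, no final threshold changes, and the stated design (α 0.0466, power 0.9017) is restored.

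### The stage 2B stopping boundary (7 or fewer of 11) is one too low: the 90-day survival test has a type I error of 0.234, not the stated 0.20

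*Protocol article*

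**What the plan says.** All of this is in the protocol article, under Sample size justification, part (B).

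- Design: "An optimal three-stage design", testing a null 90-day survival of 73% or less against an alternative of 88% or more.
- Error rates: "The significance level is set at 0.20 (target α=0.2)" and "The power is set at 80% (target β=0.2)".
- Stage 1B, after 3 transplants: "the trial will stop early (concluding p≤0.73) if there are fewer than two patients achieving 90-day survival". Otherwise "an additional eight transplantations will be performed", making 11.
- Stage 2B, after 11 transplants: "the trial will stop early (concluding p≤0.73) if there are 7 or fewer successes". With 8 or more survivors, 11 further transplants follow, making 22.
- Stage 3B: the trial succeeds with 18 or more survivors of 22.

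The 11-patient boundary is given from both sides (7 or fewer stops, 8 or more continues), so the wording is not ambiguous. No other part of the text gives a different value. Figure 2, the trial schema, is not available in the copy reviewed.

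**The concern.** A three-stage single-arm design is fully determined by its sample sizes and boundaries. Its α and power follow from them and can be compared with the stated values. Here they do not agree, and the middle boundary is the number that fails to fit.

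Outcome B is the co-primary on which transplantation of these livers is judged a success, and the Discussion presents the staged design as a safety feature. If the boundary is too lenient, a programme whose true 90-day survival is only the undesirable 73% is declared successful more often than the plan says. It also passes the 11-patient look more often. The boundary case is telling: 8 of 11 is 72.7%, just below the rate the plan calls undesirable, yet it leads to 11 more transplants.

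**Working it through.** **Inputs (protocol article, Sample size justification, part B).** p0=0.73; p1=0.88; stage sizes 3, 8 and 11 (cumulative 3, 11, 22); continue at ≥2 of 3 and at ≥8 of 11; succeed at ≥18 of 22.

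**Formula.** Let b(n, x, p) be the binomial probability of x survivors among n. The probability of passing stage 1 and having k survivors among 11 is

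f(k) = Σ over s = 2, 3 of b(3, s, p) × b(8, k−s, p).

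With lower continuation limit c at the second look (c = 8 as written),

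P(success) = Σ over k ≥ c of f(k) × P(at least 18−k survivors among the last 11).

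This is the type I error at p=0.73 and the power at p=0.88.

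**Type I error at p=0.73**

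| k of 11 | f(k) | needed of last 11 | probability | product |
|---|---|---|---|---|
| 8 | 0.2222 | 10 | 0.1590 | 0.0353 |
| 9 | 0.2232 | 9 | 0.3951 | 0.0882 |
| 10 | 0.1276 | 8 | 0.6570 | 0.0839 |
| 11 | 0.0314 | 7 | 0.8507 | 0.0267 |

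- As written (k = 8 to 11): **0.2340**, against the stated 0.20.
- Continuing only at 9 or more (k = 9 to 11): **0.1987**.

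**Power at p=0.88.** The products for k = 8, 9, 10, 11 are 0.0533, 0.2046, 0.3551 and 0.2436. As written the sum is 0.8566; from k = 9 it is 0.8033.

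**Expected sample size under p0.** The probability of stopping at stage 1 is 0.0197 + 0.1597 = 0.1793, so

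E(N) = 3 + 8 × 0.8207 + 11 × P(reach stage 3).

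- As written: P(reach stage 3) = 0.6044, E(N) = 16.2.
- Continuing at 9 or more: P(reach stage 3) = 0.3822, E(N) = 13.8.

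**Could another reading rescue α=0.20?**

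| Change to the written rule | α | power |
|---|---|---|
| Stage 1: continue at ≥1 of 3 | 0.245 | 0.878 |
| Stage 1: continue only at 3 of 3 | 0.149 | 0.633 |
| Stage 2: continue at ≥7 of 11 | 0.238 | 0.862 |
| **Stage 2: continue at ≥9 of 11** | **0.199** | **0.803** |
| Stage 2: continue at ≥10 of 11 | 0.111 | 0.599 |
| Final: succeed at ≥19 of 22 | 0.114 | 0.721 |
| No interim stopping | 0.252 | 0.885 |

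Even with p0 lowered to 0.72, the written rule gives 0.204. Enumerating every set of boundaries on 3/11/22 leaves exactly one with α≤0.20 and power≥0.80: stop at ≤1 of 3, stop at ≤8 of 11, succeed at ≥18 of 22.

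**Is that the optimal design?** A search over three-stage designs with a first stage of up to 15 and a total of up to 26, subject to both targets, ranked by E(N) under p0, puts this design first at 13.77; the next best is 13.86. A further search over totals of 23 to 32 found nothing below 14.09.

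**Comparison with part A.** The Simon two-stage design (at least 8 of 24, then at least 22 of 53; 30% v 50%) gives α=0.047 and power=0.902, in line with the stated 0.05 and 0.90. The mismatch is confined to part B.

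**The case against.** The arithmetic is hard to dispute; its weight can be.

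- *The excess is small and α is called a target.* It is 3.4 points on an already liberal 20%, power is above target, and the final criterion of 18 of 22 is not shown to be wrong. The only affected path is exactly 8 of 11 followed by at least 10 of the last 11, ending at 18 or 19 of 22 (82–86%). This is fair on size. It does not excuse the mismatch, because a rule with the same sample sizes meets both targets; discreteness is not the cause.
- *Fewer recipients would be spared than expected N suggests.* Planned interim assessments allows recruitment to continue while the 11-patient outcome matures. This stands. Assuming 22 transplants spread evenly over the 24 months given under Trial status, about 22/24 × 3 ≈ 3 would be done in the 90-day wait. The expected saving at 73% survival then falls from 0.222 × 11 = 2.4 patients to about 0.222 × 8 = 1.8.
- *Other safeguards exist.* Entry is suspended after a death pending review, and the Data Monitoring Committee sees safety data and can meet in an emergency. True, but none of these enters the stated error rates.
- *A transcription slip is an inference.* Also true: the text proves only that boundary and α disagree. The inference is strong, since the three sample sizes and the other two boundaries all coincide with the optimal design.

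**Conclusion.** The plan is wrong as written. The stated rule has a type I error of 0.234 rather than 0.20, power of 0.857 rather than 0.80, and an expected sample size under the null of 16.2, against 13.8 for the design that is optimal for these inputs. At a true survival of 73%, the chance of having stopped by the 11-patient look is 39.6% (1 − 0.6044) instead of 61.8% (1 − 0.3822). The middle boundary is very probably one too low.

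These figures assume independent outcomes with a common survival probability, 90-day status known for every recipient, and binding stopping rules. If the interim rules were ignored altogether, the type I error would rise to 0.252, further from the stated value.

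**What to change.** Reconcile the boundary with the error rates in one of two ways, and align Figure 2 if it carries the boundary.

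1. **Change stage 2B** to stop at 8 or fewer of 11 and continue at 9 or more. Everything else stays, and both the stated error rates and the word optimal then hold (α=0.199, power=0.803). The cost is more early stopping of a good programme: at 88% survival the cumulative chance of stopping by 11 patients rises from 6.3% (1 − 0.9367) to 15.0% (1 − 0.8497).
2. **Keep 7 of 11**, state α=0.234 and power=0.857, and remove the word optimal. This costs nothing operationally, but openly accepts the higher false-success risk.

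Either needs only a short text amendment and leaves the maximum of 22 transplants unchanged. Recruitment opened in October 2016, so the first option should be adopted only if the 11-patient outcomes are not yet known; otherwise the change could be data-driven, and restating the error rates is the cleaner course.
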